# The efficacy and safety of bilateral synchronous transcutaneous auricular vagus nerve stimulation for prolonged disorders of consciousness: a multicenter, double-blind, stratified, randomized controlled trial protocol

**DOI:** 10.3389/fneur.2024.1418937

**Published:** 2024-05-31

**Keywords:** transcutaneous auricular vagus nerve stimulation, coma recovery scale-revised, heart rate variability, randomized controlled trial, disorders of consciousness

## Abstract

**Background:**

Treatment of disorders of consciousness (DOC) poses a huge challenge for clinical medicine. Transcutaneous auricular vagus nerve stimulation (taVNS) is a non-invasive neuromodulation method, which shows potential in improving recovery of DOC. However, the evidence came from single-center, small-sample randomized controlled trial, which is insufficient to form a conclusion. Thereby, we propose a prospective, multicenter, double-blind, stratified, two-arm randomized controlled trial protocol to investigate the efficacy and safety of bilateral synchronous taVNS for treatment of DOC.

**Methods:**

We aim to recruit 382 patients with prolonged DOC, and divide them into an active stimulation group and a sham stimulation group. The patients in the active stimulation group will receive bilateral synchronous taVNS with a 200 μs pulse width, 20 Hz frequency, and personal adjusted intensity. The sham stimulation group will wear the same stimulator but without current output. Both groups will receive treatment for 30 min per session, twice per day, 6 days per week lasting for 4 weeks. The clinical assessment including Coma Recovery Scale-Revised (CRS-R), Full Outline of Unresponsiveness (FOUR), Glasgow Coma Scale (GCS), and Extended Glasgow Outcome Scale (GOS-E) will be conducted to evaluate its efficacy. Heart rate variability (HRV), blood pressure, and adverse events will be recorded to evaluate its safety.

**Discussion:**

These results will enable us to investigate the efficacy and safety of taVNS for DOC. This protocol will provide multicenter, large-sample, high-quality Class II evidence to support bilateral synchronous taVNS for DOC, and will advance the field of treatment options for DOC.

**Clinical trial registration:**https://www.chictr.org.cn/showproj.html?proj=221851, ChiCTR2400081978.

## Introduction

Disorders of consciousness (DOC) refer to the state in which an individual’s response to external stimuli is reduced or even non-responsive. The DOC caused by diseases such as traumatic brain injury, intracerebral hemorrhage, cerebral infarction, and cardiac arrest, which are manifested as alterations in arousal and/or awareness (1), including coma, vegetative state/unresponsive wakefulness syndrome (VS/UWS), and minimally conscious state (MCS) (1, 2). Coma is defined as a state with completely lack of arousal (eyes closed) and awareness (3). While VS/UWS is defined as preserved arousal (eyes open) but without awareness (4). MCS is defined as the minimal, reproducible, but inconsistent state of awareness (5), without (MCS-) or with (MCS+) evidence of language function (6). In recent years, with the rapid development of modern medicine, the increasingly successful treatment for severe brain injury patients has led to a continuous increase in the number of patients falling into long-term survival with DOC (7). A DOC lasting up to 28 days is termed as a prolonged DOC (pDOC) (8). It poses a huge challenge for clinical medicine, as well as a huge pressure on families and society (7).

Numerous researchers and clinicians are devoting to improve the conscious state of patients and accelerate their recovery. Medications (amantadine, midazolam, intrathecal baclofen, etc.), invasive and non-invasive brain stimulation (deep brain stimulation, spinal cord stimulation, transcranial direct current stimulation, repeated transcranial magnetic stimulation, etc.), sensory stimulation (motor-based therapy, auditory-based training, music therapy, and multi-sensory training), hyperbaric oxygen and other treatments have been used to achieve better rehabilitation goals (9). The evidence-based basis for these treatments has been continuously improved in recent years (10, 11). Vagus nerve stimulation (VNS) is a type of brain stimulation technique, which has been considered as one of the latest neuromodulation methods benefit to patients with DOC.

The first clinical application of VNS was the treatment for intractable partial seizures (12). Its clinical application was approved by the Food and Drug Administration (FDA) in 1997 (13). Currently, besides intractable partial seizures, the FDA has approved VNS for medication-resistant depression (14), episodic cluster headaches (15) and moderate-to-severe upper extremity motor impairments following chronic ischemic stroke (16).

According to the International Consensus Based Review and Recommendations for Minimum Reporting Standards in Research on Transitional VNS (Version 2020) (17), there are four currently accepted VNS methods: cervically implanted VNS (iVNS), transcutaneous cervical VNS (tcVNS), transcutaneous auricular VNS (taVNS), and percutaneous auricular VNS (paVNS). Among them, taVNS is a safe, non-invasive, and easy-to-use treatment option, compared to iVNS (18). The first use of VNS for DOC was published in 2017 with a case report (19). A VS/UWS due to cardiac arrest developed to MCS after 4 weeks of taVNS. In the same year, another case report also reported that a patient with VS/MCS developed to MCS after 4 weeks of iVNS (20). Subsequently, 5 (21), 10 (22), and 14 (23) patients with DOC were treated with VNS in 3 case series (1 iVNS and 2 taVNS). These case series indicated that VNS improved the behavioral responses (conscious state) of patients and was safe and feasible for DOC.

However, these uncontrolled case reports (19, 20) and case series (21–23) only provided weak Class IV and Class V evidence of treatment efficacy. It cannot be ruled out that the impacts are from spontaneous recovery, especially considering the acute to subacute background of the enrolled patients. Recently, we provided the highest level of evidence for the efficacy and safety of VNS for DOC with a single-center double-blind randomized controlled trial (RCT) (28 active versus 29 sham stimulation) (24). It indicated that 4 weeks’ taVNS significantly improved the Coma Recovery Scale-Revised (CRS-R) score of MCS patients, and without significant side effects. In order to further confirm and validate the efficacy and safety of taVNS, as well as to provide more comprehensive and reliable evidence, we propose here a multicenter, double-blind, stratified, two-arm RCT.

## Methods and analysis

### Study design

This is a prospective, multicenter, double-blind, stratified, two-arm RCT. This study protocol is designed according to the Declaration of Helsinki. It has been approved by the Ethics Committee of the Affiliated Rehabilitation Hospital of Nanchang University (SFYYXLL-PJ-2023-KY015) and has been registered at the Chinese Clinical Trial Registry (ChiCTR2400081978, https://www.chictr.org.cn/showproj.html?proj=221851). As the participants are patients with DOC, informed consent will be obtained from their legal representatives. The study design and final report will follow the Consolidated Standards of Reporting Trials (CONSORT) statement and its extension to non-pharmacologic treatment interventions. Figure 1 shows the study flowchart.

**Figure 1 fig1:**
[figure not shown]
Study flowchart. pDOC, prolonged disorders of consciousness.

### Population

The study participants are patients with pDOC who will be recruited from 8 large and experienced centers of rehabilitation medicine: (1) Affiliated Rehabilitation Hospital of Nanchang University; (2) the First Affiliated Hospital of Nanchang University; (3) Ganzhou People’s Hospital; (4) the First Affiliated Hospital of Gannan Medical College; (5) Fuzhou First People’s Hospital; (6) Xinyu People’s Hospital; (7) Jiujiang First People’s Hospital; (8) Nanchang Hongdu Hospital of Traditional Chinese Medicine. Patients will be screened by trained medical personnel based on the inclusion and exclusion criteria.

Inclusion criteria: (1) Aged 18 to 65 years old; (2) Acquired brain injury patients with clear etiology; (3) Diagnosed as VS/UWS or MCS (based on 5 consecutive days of CRS-R evaluation, performed by two individuals, and consulted with a third party in case of dispute); (4) Fall in DOC up to 28 days; (5) The skin at the site of stimulation is intact; (6) Sign informed consent.

Exclusion criteria: (1) Patients whose vital signs are unstable; (2) Patients with active intracranial hypertension; (3) Patients with pacemakers, cochlear implants, or metal implants in the brain; (4) Patients with a history of cerebral nervous system disease prior to brain injury; (5) Patients with deep sedation caused by general anesthesia (e.g., propofol) or central sedatives (e.g., benzodiazepines, opioids); (6) Patients with bradycardia, atrial fibrillation, or atrioventricular block; (7) Pregnant patients.

Withdrawal criteria: (1) Recurrent seizures are difficult to control during treatment; (2) Life-threatening diseases (such as severe intracranial infections and cerebral hernia) occur; (3) Patients who consistently exhibit signs of pain below the threshold of given stimulus intensity; (4) Proactively exit.

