### Randomization and allocation concealment

The grouping scheme adopts stratified block randomization. Specifically, patients are first stratified according to the research center and then stratified according to the degree of DOC (VS/UWS or MCS). Then, patients are randomized 1:1 in variable block sizes, with stratification balancing by research center and degree of DOC. The randomization procedure is performed by independent statistical experts who are not involved in the study’s implementation or statistics. The study secretary places the generated random numbers and the grouping outcomes separately into opaque envelopes and sends them to each participating sub-center. After patients are confirmed to be enrolled, the sub-center doctors sequentially open the numbered envelopes to complete the grouping.

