### Data collection

After enrollment, demographics and baseline data of patients in both groups will be collected, including gender, age, cause of injury, duration of DOC, CT results (subarachnoid hemorrhage, hydrocephalus), pupillary light reflex (none, one side, both sides), cranial surgery (with or without), tracheotomy (with or without), multiple injuries (with or without), initial CRS-R, Full Outline of Unresponsiveness (FOUR), and Glasgow Coma Scale (GCS) scores.

Patients in both groups will be evaluated via CRS-R, FOUR, and GCS scores after 2 weeks of treatment and at the end of treatment (after 4 weeks of treatment). The improvement in the CRS-R scores at the end of treatment is the primary outcome. Extended Glasgow Outcome Scale (GOS-E) scores will be followed up at 3 and 6 months after the end of treatment. During follow-up, if the patients are still in the hospital, they will be evaluated in the ward. If the patients are discharged, they will be evaluated via structured phone interviews with themselves, their family members, or caregivers. According to reports, the assessment of GOS-E via phone is a valid alternative to face-to-face interviews when face-to-face contact is not possible. The level of agreement (Cohen’s weighted κ) between the two is good (27). The evaluation process during treatment and follow-up is shown in Figure 3. The total length of hospital stay and mortality during treatment and follow-up will also be recorded.

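### Inclusion criterion 4 and the definition of prolonged DOC give 28 days as a maximum duration, which contradicts the prolonged-DOC population the trial says it enrols

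*Protocol article*

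**What the plan says.** Under Population, the article opens with the statement that "The study participants are patients with pDOC who will be recruited from 8 large and experienced centers of rehabilitation medicine". Inclusion criterion 4 in the same section then sets the duration requirement: "Fall in DOC up to 28 days". No other inclusion or exclusion criterion sets a duration.

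The Introduction defines the term with the same wording: "A DOC lasting up to 28 days is termed as a prolonged DOC (pDOC" (the abbreviation closes the sentence). That definition follows directly on a sentence about the "continuous increase in the number of patients falling into long-term survival with DOC".

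The title, the Methods part of the abstract, the Sample size section and the section on blinding also describe the participants as having prolonged DOC. Duration of DOC is recorded at baseline (Data collection lists "cause of injury, duration of DOC, CT results"). It is not a randomisation factor: the scheme uses "stratification balancing by research center and degree of DOC".

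**The concern.** A limit of up to 28 days is a ceiling. A ceiling alone cannot select a prolonged condition, so the eligibility rule and the named population point in opposite directions. The Introduction does not settle the matter, because a reader who turns to it for the definition finds the same ceiling.

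This is an operative rule for screeners at eight centres. If it were applied as worded, or read differently from centre to centre, the trial would enrol a population other than the one in its title. It would then be unclear to which patients the result applies. Eligibility decisions could also be disputed afterwards, because a patient accepted under one reading is a deviation under the other.

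**Working it through.** The question is one of wording, so the check sets the statements side by side and then asks whether any figure in the plan depends on them.

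**1. The two readings, with d = days in DOC at enrolment**

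| Reading | Condition | d = 10 | d = 28 | d = 29 or more |
|---|---|---|---|---|
| Criterion 4 as worded | d ≤ 28 | eligible | eligible | not eligible |
| Minimum, at least 28 days | d ≥ 28 | not eligible | eligible | eligible |
| Minimum, more than 28 days | d > 28 | not eligible | not eligible | eligible |

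The literal rule overlaps with the second row on day 28 only, and with the third row not at all.

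**2. Which reading the rest of the article supports**

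- Criterion 4 and the definition in the Introduction agree with each other. The contradiction is between both of them and the word prolonged, as used in the title, abstract, Population and Sample size sections.
- The definition sits next to a sentence about long-term survival, and recruitment is from rehabilitation centres. Both fit a minimum and not a maximum.
- Nowhere does the article's text say at least, more than or beyond 28 days. The flowchart image (Figure 1) could not be checked.

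The context therefore indicates a minimum, but the reader has to infer it against the wording of the rule.

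**3. Whether the sample size depends on it**

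Inputs, all from the Sample size section: means 10.93 and 9.28, SDs 4.99 and 4.38, power 90%, α 0.05, equal groups, 10% loss.

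- Difference: 10.93 − 9.28 = 1.65
- Pooled SD: √[(4.99² + 4.38²)/2] = √[(24.900 + 19.184)/2] = 4.695
- Two-sided normal formula: n = 2 × (1.960 + 1.282)² × 4.695² / 1.65², which rounds up to 171 per group. The t-test version gives 171.1, rounded up to the stated 172.
- Power at 172 per group: 90.3%
- Loss: 2 × 172 = 344, and 344/0.9 = 382.2, stated as 382

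The plan's figures reproduce. Duration of DOC enters none of these steps, so rewording the criterion changes nothing here.

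**4. Whether the comparison between arms depends on it**

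Patients are randomised 1:1 against sham within strata of centre and degree of DOC. Whatever population a centre admits, it is divided between the arms by the same random process. Even if centres read the criterion differently, the difference lies between strata and not between arms.

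**The case against.** The strongest reply is that this is a translation slip whose intent is obvious. The Population section states that "The study participants are patients with pDOC" before it lists the criteria, and the literal reading would defeat the trial's own title. There is no evidence that any centre would apply it literally, and the full protocol used at the sites may be worded correctly. These points stand as to cause, and they make literal application unlikely. They do not repair the text: the article states a bound, twice, in the direction opposite to the population it names. This is an incorrect statement and not a detail left out of a condensed article.

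A second reply is that other criteria limit very early enrolment even on the literal reading. Patients must be diagnosed as VS/UWS or MCS over five consecutive days of CRS-R assessment. Unstable vital signs, active intracranial hypertension and deep sedation are exclusions. That is correct, and it tempers any claim that the trial would fill with acute patients. None of these criteria sets a 28-day minimum, however, and none readmits patients beyond day 28.

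A reader might also infer that early patients would bias the result through spontaneous recovery, since the Introduction discounts earlier evidence "especially considering the acute to subacute background of the enrolled patients". The documents do not support this. That remark concerns uncontrolled case reports and case series. Here spontaneous recovery would be expected in both arms of a randomised, sham-controlled comparison.

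**Conclusion.** The point holds as a contradiction in the text. Criterion 4 and the definition in the Introduction give the 28-day bound as a maximum, while the trial is described throughout as one in prolonged DOC. On the literal reading the rule excludes essentially the whole population in the title.

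The consequence is limited to an unclear target population and unclear generalisability, with avoidable doubt about eligibility at the centres. There is no bias between arms and no change to 172 per group or 382 in total. Any extra variability from mixed durations cannot be quantified from the article.

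It would go too far to say that the sponsor chose to study patients in the first 28 days; the context makes a language error more likely. The conclusion that a minimum was meant is an inference from the word prolonged, the long-term-survival context and the rehabilitation setting. Whether day 28 itself qualifies cannot be decided from the article.

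**What to change.** Reword inclusion criterion 4 so that the 28-day bound is explicitly a minimum duration of DOC at enrolment, and correct the definition in the Introduction to match. The sponsor should confirm whether the bound is at least or more than 28 days against the full protocol and the registered criteria, and should notify all eight centres of the confirmed wording.

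The cost is one line in each of two places, a check against the registration and a note to the centres. No change to the sample size, randomisation or analysis is needed.

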### Sample size

The required sample size was calculated based on the results of our previous single-center RCT (24). In which, the difference of total CRS-R score between the taVNS group and the sham stimulation group after treatment was 10.93 ± 4.99 vs. 9.28 ± 4.38. We set the test power (1-β) to be 90%, the type I error rate (α) to be 0.05, and the group allocation of the two groups to be equal. The calculated sample size was N1 = N2 = 172. Considering that 10% of patients will be lost during follow-up, a total of 382 patients with pDOC will eventually be enrolled.

### Randomization and allocation concealment

The grouping scheme adopts stratified block randomization. Specifically, patients are first stratified according to the research center and then stratified according to the degree of DOC (VS/UWS or MCS). Then, patients are randomized 1:1 in variable block sizes, with stratification balancing by research center and degree of DOC. The randomization procedure is performed by independent statistical experts who are not involved in the study’s implementation or statistics. The study secretary places the generated random numbers and the grouping outcomes separately into opaque envelopes and sends them to each participating sub-center. After patients are confirmed to be enrolled, the sub-center doctors sequentially open the numbered envelopes to complete the grouping.

### Intervention protocol

After grouping, both groups will undergo identical routine rehabilitation therapy and nursing. The active stimulation group will receive bilateral synchronized taVNS treatment (JY-VNS-200, Jingyi Medical Technology Co., Ltd., Jiangxi, China, Figure 2A). Electrotherapy is performed through a pair of metal electrodes, which are placed on the headphone-like stimulating end. The metal electrodes correspond directly to the cymba conchae and the cavum conchae (Figure 2B). Before treatment, the stimulation sites are thoroughly cleansed with alcohol to minimize impedance and ensure optimal conductivity. Treatment parameters: sine wave, 200 μs pulse width, 20 Hz frequency, 2 mA initial current intensity, 30 s on/30 s off cycle. The stimulation intensity will be gradually adjusted downwards in steps of 0.5 mA based on the patient’s tolerance (pain perception). To accurately distinguish pain from non-pain, the Nociception Coma Scale-Revised (NCS-R) will be utilized both initially and throughout the stimulation process, with a threshold of 4 points (25, 26). If the NCS-R score indicates pain (i.e., a score of ≥4), the stimulation intensity will be promptly reduced by 0.5 mA, and the NCS-R evaluation will be repeated. Patients who continue to exhibit signs of pain below the 0.5 mA threshold will be excluded from the study. To guarantee optimal contact between the electrodes and the ear skin, as well as to minimize the risk of electric burns, the device incorporates both an alarm function and a protection mechanism. These safety features will be activated whenever the electrodes fail to maintain adequate contact with the ear skin, such as when impedance exceeds 10 K Ω or the single pulse energy surpasses 8 mJ.

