**Figure 2 fig2:**
[figure not shown]
**(A)** Bilateral synchronous taVNS device; **(B)** stimulation sites and electrodes.

The device is presented with Mode A and Mode B. One is active stimulation, and the other is sham stimulation with no current output. Both modes exhibit identical screen displays and button operations (the current intensity can be adjusted, while other parameters are fixed to the values mentioned above). This makes researchers and device operators unaware of which stimulation is the active one. The two groups will receive treatment for 30 min per session, twice a day, 6 days a week for 4 weeks. The above treatment parameters and time refer to our previous single-center study (24) and peer studies (19, 23, 25). Bilateral synchronous taVNS will be performed at the same time before the start of the routine rehabilitation therapy in the morning and afternoon every day, under the operator’s continuous monitoring.

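### Randomised patients whose pain signs persist are removed from the study, not only from stimulation, and these losses are likely to fall mainly on the active arm

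*Protocol article*

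**What the plan says.** The order of events is clear. Under Randomization and allocation concealment, "After patients are confirmed to be enrolled, the sub-center doctors sequentially open the numbered envelopes to complete the grouping". The Intervention protocol section then begins: "After grouping, both groups will undergo identical routine rehabilitation therapy and nursing". Stimulation starts at "2 mA initial current intensity" and is lowered in steps of 0.5 mA when the Nociception Coma Scale-Revised (NCS-R) indicates pain. That scale "will be utilized both initially and throughout the stimulation process, with a threshold of 4 points". The section then gives the rule at issue: "Patients who continue to exhibit signs of pain below the 0.5 mA threshold will be excluded from the study".

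The Population section lists the same event as withdrawal criterion (3) in different words: "Patients who consistently exhibit signs of pain below the threshold of given stimulus intensity". It stands beside recurrent seizures that are hard to control, voluntary exit, and "Life-threatening diseases (such as severe intracranial infections and cerebral hernia) occur". None of these criteria is limited to one arm.

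On the device modes, the Intervention protocol says: "One is active stimulation, and the other is sham stimulation with no current output". Displays and controls are the same in both modes, so the operator is blind. The primary outcome, under Data collection, is improvement in CRS-R at the end of the 4 weeks, and the first post-baseline score is due at week 2. The Statistical analysis section names a linear mixed-effects model for change over time.

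**The concern.** Titration takes place after allocation, and its trigger is a reaction to the allocated treatment. Current can cause pain in one arm and cannot in the other. If patients who react leave the study, the two arms at week 4 are no longer the two groups that were randomised.

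The loss may also be related to the outcome. According to the Discussion, NCS-R scores motor, verbal and facial responses. It is reasonable, though not stated, that patients who reach the threshold are more responsive and so have higher CRS-R scores. The seizure and life-threatening-disease criteria remove patients with poor outcomes. If those events differed by arm, that loss would favour the arm with more of them.

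At stake are the week-2 and week-4 CRS-R scores of the patients removed. If these are not taken at the time, no later analysis can recover them. The 10% allowance in the Sample size section covers the number of patients lost, not selective loss.

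**Working it through.** **1. The plan's own figure.** From the Sample size section, the difference is 10.93 − 9.28 = 1.65, and the SD is √((4.99² + 4.38²)/2) = 4.695. With 90% power and two-sided α = 0.05, the normal approximation gives 171 per arm and the t-based calculation gives 172, as stated. Allowing for 10% loss, 344/0.9 = 382.2, against the stated 382. The sample size is not in error.

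**2. What the titration ladder implies.** Starting at 2 mA with steps of 0.5 mA, the levels are 2.0, 1.5, 1.0, 0.5 and then 0. There are two readings of the exclusion rule:

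- Pain still present *at* 0.5 mA, the lowest active level. Current-evoked pain is then possible in the active arm and impossible in sham, so exclusions are expected to be unequal.
- Pain present *below* 0.5 mA, as literally written. The only remaining step is 0 mA, where active and sham deliver the same output, so exclusions would be roughly balanced.

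Withdrawal criterion (3) refers to a threshold of the given stimulus intensity and does not settle which is meant.

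**3. Size of the bias if exclusions are active-only.** Let f be the share of the active arm excluded, and D the difference in mean CRS-R outcome between excluded and retained patients. The full-arm mean is (1 − f) × retained mean + f × excluded mean, so the retained mean differs from the full-arm mean by f × D. The document gives neither f nor D, so both are assumed, with no sham exclusions. For precision, each arm has 191 × 0.9 = 171.9 patients, the active arm is multiplied by (1 − f), and the SD is 4.695.

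| f (patients of 191) | D, points | Bias = f × D | % of 1.65 | Two-sided type I error | Power if bias is against active |
|---|---|---|---|---|---|
| 1% (1.9) | 1 | 0.01 | 0.6 | 0.050 | 0.90 |
| 1% (1.9) | 4 | 0.04 | 2.4 | 0.051 | 0.89 |
| 5% (9.6) | 1 | 0.05 | 3.0 | 0.051 | 0.88 |
| 5% (9.6) | 4 | 0.20 | 12.1 | 0.068 | 0.81 |
| 10% (19.1) | 1 | 0.10 | 6.1 | 0.054 | 0.85 |
| 10% (19.1) | 4 | 0.40 | 24.2 | 0.120 | 0.67 |

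With D = 0, power stays at about 0.89 to 0.90. If f and D are the same in both arms, the bias is about zero.

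**4. Limit of this calculation.** The SD of 4.695 is for post-treatment scores, whereas the primary outcome is improvement. The document gives no SD of change, so the type I error and power columns are only a guide. The sign is also open: patients who are more responsive at baseline have higher final scores but need not improve more.

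**The case against.** A reader might infer that the loss comes from the active arm alone. The document does not support that. Criterion (3) applies to both arms, blinded operators use the same controls in both modes and cannot confine the rule to one of them, and NCS-R scores behaviour that could reach 4 spontaneously or with handling in a sham patient. *Mainly active* is as far as the text goes, and under the literal 0 mA reading even that weakens.

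A reader might also infer that these patients are certain to be missing from the primary analysis. The article names no analysis set, and Data management refers to a predetermined statistical analysis plan that is not shown. Data collection schedules assessments for patients in both groups and makes no exception for those withdrawn. This stands as far as the analysis set goes. It does not answer the point about conduct: exclusion from the study is what the article states, and an analysis plan cannot supply scores that were never taken.

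Third, the mixed model may repair part of the loss. If baseline CRS-R is in the response vector, a patient with only a baseline score still contributes, and if baseline captures the responsiveness that led to exclusion, the missing scores are missing at random. This stands in part. The article does not say how baseline enters the model, a patient removed at the first session has no post-baseline score, and any dependence on outcome beyond baseline would remain.

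Finally, an arm difference in seizures or life-threatening disease is conjecture, since the article describes its listed adverse events as largely unrelated to taVNS. That is fair. Those criteria matter here because they use the same all-or-nothing withdrawal, not because an imbalance has been shown.

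**Conclusion.** The point holds as a flaw of conduct and wording. Randomised patients are removed from the study, rather than only from stimulation, on a post-randomisation trigger that is likely to occur mainly, though not only, in the active arm and may be related to responsiveness. The two statements of the pain rule do not agree and must be reconciled.

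No definite bias can be claimed. Under the assumed active-only exclusion of 1–10% and a difference of 1–4 points, it runs from negligible to about a quarter of the planned effect, before any recovery by the model. Balanced exclusions would bring it close to zero. The net direction is unknown. This is a low-cost improvement worth making before scores are lost, and it is not a demonstrated failure of the primary comparison.

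**What to change.** Leave every rule for stopping stimulation as it is, and separate *stimulation stopped* from *left the study* in both the withdrawal criteria and the Intervention protocol section.

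- Any randomised patient whose stimulation is stopped keeps the assessments already scheduled: CRS-R, FOUR and GCS at weeks 2 and 4, and GOS-E at 3 and 6 months after treatment, unless consent is withdrawn.
- State that the primary analysis includes all randomised patients in the arm assigned.
- Report the number and timing of stops for pain by arm.
- Reconcile the two wordings of the pain rule so that the current level it refers to is unambiguous. Which level that should be is for the investigators and is not proposed here.

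The cost is a change of wording and some follow-up of patients no longer being stimulated, at visits already planned. The downside is slight dilution of the estimated effect, because patients who received little stimulation stay in the active arm.
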